#### **13.2. Selection of subjects for analysis**

In this study, all enrolled cases, all eligible cases, and all treated cases are defined as follows: “all treated cases” are used for safety evaluation in the final analysis, and “all enrolled cases” or “all eligible cases” are used for efficacy evaluation.

1) All registered cases

The population of registered patients, excluding duplicate or mis-registered patients.

2) All eligible cases

The population excluding “ineligible cases” considered by the group review from the total enrolled cases. However, for periodic monitoring and analysis at the time of conference presentation prior to the submission of the final analysis report, “ineligible cases” may not be included in the total eligible cases with the consent of the study office.

3) All treated cases

All enrolled patients who received some or all of the protocol treatment.

### 13.3. Basis for setting the number of cases

When conducting an analysis of the primary endpoint using the “Definition of the percentage of treatment completion” in the “Evaluation Methodology” section of the endpoints, cases of protocol discontinuation due to relapse should be treated as discontinuations (dropouts), and are not appropriate as eligible cases for the analysis. The percentage of patients who “completed treatment” was calculated based on the number of patients who were excluded from the total number of eligible cases.

In the LOGIK0601 study of S-1 80 mg/m^2/day 2-week administration followed by 1-week rest (6 months administration) in patients with Stage IB or more completely resected non-small cell lung cancer, treatment completion was 56.7% (95% CI: 37.4–74.5, relative dose rate 73.9) and the completion rate in patients 70 years and older was 42.9% (6/14). On the other hand, although the data are not available for elderly patients, the use of S-1 every other day (1 year) after gastric cancer surgery resulted in 19.6% and 13.7% higher compliance and RDI, respectively, than the usual administration regimen (1 year) (91.8% vs 72.2% and 81.2% vs 67.5%, respectively).

Assume that 55% of the patients in the better group and 40% of the patients in the worse group complete treatment for 6 months with the biweekly or 2-week administration followed by 1-week rest method. Based on the selection theory, 37 cases in each group are required to detect this 15% difference with a 90% probability of correct selection. Assuming dropout cases, a total of 100 cases are required. The expected annual enrollment is 50 cases, and the enrollment period is 2 years.

In order to achieve ITT analysis, Kaplan-Meier curves for the actual total number of days of S-1 administration in each case were drawn for all enrolled patients. An event is considered to have occurred at the time of discontinuation due to S-1 toxicity. If the drug is discontinued due to complications (recurrence, second cancer) that are not directly related to S-1, the event is considered to have occurred at that time.

The continuation rate calculated from the Kaplan-Meier curve will also be evaluated as a secondary measure of compliance with the study treatment.

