### 0.3. Treatment

#### Arm A: alternate-day administration of S-1

S-1 is administered on Mondays, Wednesdays, Fridays, and Sundays and repeated until one of the criteria for discontinuation of treatment is met. Treatment with alternate-day administration of S-1 should be continued for 1 year counting from the date of the first S-1 administration.

If administration cannot be started more than 28 days after the last day of administration, this study treatment will be discontinued (day 1 will be the day after the last administration). The same day of the week 4 weeks after the last administration is acceptable).

[figure not shown]

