#### Arm B: Daily administration of S-1 for 2 weeks followed by 1-week rest

S-1 is taken orally every day for 14 days (after dinner on Day 1 to after breakfast on Day 15), followed by a 7-day rest period, repeated every 3 weeks as a course. This is repeated every 3 weeks for a total of 12 months from the start date of the protocol treatment. No new course will be started after the same calendar day 12 months after the start date of the protocol. The final course of treatment should be administered until the equivalent of day 14. If administration cannot be started more than 28 days after the last day of administration, this study treatment will be discontinued (day 1 will be the next day after the last administration). The same day of the week 4 weeks after the last administration is acceptable).

Administration is repeated until one of the criteria for discontinuation of study treatment is met.

[figure not shown]

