##### Administration Schedule

The first dose of S-1 should be initiated on Monday, Wednesday, Friday, or Sunday (the specified day of the week); Day 1 is defined as the day on which S-1 is initiated.

If S-1 cannot be administered after breakfast, it may be started after dinner. Even if S-1 is started after dinner, the day should be defined as the day on which S-1 is initiated, and the next dose should be taken on the specified day of the week.

(e.g., if taken on Friday evening, the next dose will be given on Sunday morning)

S-1 should be administered on Mondays, Wednesdays, Fridays, and Sundays and should be continued until one of the criteria for discontinuation of treatment is met. **S-1 should not be administered other than the specified day.**

- If administration cannot be started more than 28 days after the last day of administration, this study treatment will be discontinued (day 1 will be the day after the last dose). The same day of the week 4 weeks after the last dose is acceptable).

[figure not shown]

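### Taken literally, the all-enrolled Kaplan-Meier continuation curve is plotted on S-1 dosing days, which accrue more slowly in Arm A by design, so it understates Arm A's continuation relative to Arm B.

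*Protocol*

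**What the plan says.** The sample-size section of the Protocol (13.3) introduces, with the aim of an ITT analysis, a continuation analysis: "Kaplan-Meier curves for the actual total number of days of S-1 administration in each case were drawn for all enrolled patients". It fixes the events as well. For toxicity, "An event is considered to have occurred at the time of discontinuation due to S-1 toxicity". For stops caused by "complications (recurrence, second cancer) that are not directly related to S-1, the event is considered to have occurred at that time". Its role is stated: "The continuation rate calculated from the Kaplan-Meier curve will also be evaluated as a secondary measure of compliance with the study treatment".

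The two schedules are set out in sections 0.3, 6.2.1 and 6.3.1. In Arm A, "S-1 is administered on Mondays, Wednesdays, Fridays, and Sundays". In Arm B, "S-1 is taken orally every day for 14 days", followed by seven days of rest, in three-week courses. Both arms are planned for one calendar year from the start of treatment (6.2.7 and 6.3.1).

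**The concern.** A Kaplan-Meier curve compares two arms fairly only if a given point on the time axis means the same thing in both. A count of dosing days does not meet that condition here, because the arms differ by design in how many dosing days a week of treatment contains. The same point on the axis falls later in calendar time in Arm A, so Arm A patients have had longer in which to stop. Suspensions also add no time on this axis.

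This is the analysis the Protocol offers to cover all enrolled patients, and its named secondary measure of compliance. The bias runs against the alternate-day regimen, which section 13.4 says the study was designed to show has better continuity. The curve could also enter decision rule (3) of section 13.4, which lists retention beyond six months among the considerations when the completion rates differ by 15 points or less.

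**Working it through.** The Protocol gives no figure for this curve. Its nearest figure, 37 per arm in section 13.3, reproduces: with completion of 55% and 40% and ties split evenly, the exact binomial probability of correct selection is 0.899 at 36 per arm and 0.902 at 37. The time axis has no bearing on it.

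**Inputs from the Protocol.** Arm A: 4 dosing days per 7 calendar days. Arm B: 14 per 21, counting each course as 14 daily doses. Planned duration: one year in both arms. Design completion rates at six months: 55% and 40%.

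**Assumptions not in the Protocol.** Full adherence while on treatment; a constant hazard of stopping; and, for the first illustration, 50% still on treatment at day 182 in both arms.

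**Accrual.**
- Rate per calendar day: A 4/7 = 0.571; B 14/21 = 0.667; ratio 6/7 = 0.857.
- By day 182: A 26 × 4 = 104. B 182 × 2/3 = 121.3 on average, or 9 × 14 = 126 counting whole courses, because day 182 is the 14th day of the ninth course.
- Over a year: A 365 × 4/7 ≈ 209; B 365 × 2/3 ≈ 243 on average, or 18 × 14 = 252 for whole courses.

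**Apparent hazard ratio under equal persistence.** One dosing day spans 7/4 calendar days in A and 3/2 in B, so the ratio is (7/4)/(3/2) = 7/6 = 1.167 against Arm A.

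**Curve values under equal persistence**, S = 0.5^(calendar day/182):

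| Dosing days | Arm A | Arm B, average accrual | Gap | Arm B, whole courses | Gap |
|---|---|---|---|---|---|
| 104 | day 182: 50.0% | day 156: 55.2% | 5.2 | day 153: 55.8% | 5.8 |
| 126 | day 220.5: 43.2% | day 189: 48.7% | 5.5 | day 182: 50.0% | 6.8 |

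**Sensitivity to the assumed persistence.** At 104 dosing days with average accrual, the gap is close to S^(6/7) − S, where S is the common six-month continuation. It is 5.6 points at 40%, 5.3 at 47.5%, 4.9 at 55% and 3.7 at 70%.

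**A real difference.** Suppose six-month calendar continuation (182.5 days) is 55% in A and 40% in B.
- At 104.3 dosing days: A 55.0%; B 0.40^(6/7) = 45.6%; gap 9.4 points.
- At 121.7 dosing days: A 0.55^(7/6) = 49.8%; B 40.0%; gap 9.8 points.

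The true 15 points appear as 9 to 10. Equivalently, with B at 40%, A would need 45.6% on the calendar scale merely for the two curves to coincide.

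On a calendar axis, equal persistence gives identical curves and the artefact disappears.

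**The case against.** The best reply is that calendar duration was meant. The text is a translation; the event sentences place events at the moment of discontinuation; and the output is called a continuation rate. Section 6.2.6 counts 43 days of treatment in Arm A where the parallel Arm B rule waits for the second course, which at 2 × 21 = 42 days suggests calendar counting. This keeps the calendar reading open but does not settle it. Section 12.2 multiplies a daily dose by a number of expected days to obtain the planned total, and under alternate-day dosing that works only if the days are dosing days. An analyst who follows section 13.3 as written would inherit the bias.

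It is also fair that the Protocol does not say the curves will be read at a common number of dosing days. Overlaying them on one axis does so implicitly, however.

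A reader might go further and infer that counting recurrence and second cancer as events is an error, since the primary endpoint in section 12.2 excludes stops for recurrence. The Protocol does not support that. Discontinuation for any cause is a legitimate measure in all enrolled patients and complements a primary rate that leaves some of them out. Nor does it favour an arm by itself: if recurrence by six months were the same in both arms, at an assumed 2% to 15% and independent of toxicity stops, a 15-point gap would become 15 × 0.98 = 14.7 to 15 × 0.85 = 12.8 points, because both curves fall by the same factor. That section 13.3 assigns no status to stops at the request of the patient or by decision of the physician is detail that an analysis plan commonly supplies.

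**Conclusion.** The point holds for the time axis only, on the literal reading of section 13.3. The 6/7 accrual ratio follows from the schedules alone. The hazard ratio of 1.167 adds full adherence and a constant hazard, and the percentage-point gaps also need an assumed level of persistence. The gap against Arm A is about 5 to 5.5 points at average Arm B accrual and reaches nearly 7 only where Arm B is read at the end of a course, so the upper figure should not be taken as typical.

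A reader might infer that the trial's main conclusion is at risk. It is not: the primary completion rate, the 37 per arm and decision rules (1) and (2) do not use this curve. Rule (3) might, but it does not name the curve, and section 12.2 separately provides completion rates at nine months and one year. This is a correction worth making to a secondary measure.

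**What to change.** In section 13.3, define time as calendar days from registration to permanent discontinuation of protocol treatment, for all enrolled patients. Count patients who never start as events at day 0. Censor those who reach the scheduled end of protocol treatment, one year from first dose, at that date. Recurrence and second cancer can remain events. If calendar duration was already intended, a sentence saying so is enough.

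The cost is a sentence or two of rewording. No treatment rule, sample size or primary analysis changes. Section 7.2 already requires the timing and reason of discontinuation in the case report form, and section 15.1 already collects administration and termination records. The contents of those forms are not shown, so it should be confirmed that they carry the dates.

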### 13.4. Decision criteria for standard treatment (S-1 administration) based on the results

This study was designed to verify that alternate-day administration is a superior method of administration with better continuity than the daily administration method. However, the difference in administration continuity alone does not necessarily mean that the true objective of adjuvant chemotherapy, namely, survival benefit, is achieved.

Therefore, at the end of the trial, the decision criteria for selecting either study arm for future Phase III trials shall be as follows.

- (1) If the six-month completion rate for both groups is less than 40%, we conclude that both groups are not promising adjuvant chemotherapy in this study.
- (2) If the completion rate of six-month treatment in one group exceeds 40% and is more than 15% higher than that in another group, we conclude that the treatment in the group with the higher completion rate of six-month treatment is the most promising adjuvant chemotherapy in the study and is more suitable for the administration of S-1 in future Phase III trials.
- (3) If the completion rate in one group is greater than 40% and the difference between one group and the other is within 15%, the two groups will not be directly compared based on retention rate numbers alone, but rather on toxicity, quality of life, convenience, cost, retention rate after 6 months, recurrence-free survival, and survival rate to determine which is more suitable as S-1 therapy in future Phase III trials.

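### Section 13.4 says the trial was designed to verify superiority of alternate-day S-1, but sections 13.3 and 13.4 set out a selection design that cannot verify it

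*Protocol*

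**What the plan says.** Section 13.4 of the protocol begins with a directional statement of what the trial was built to show: "This study was designed to verify that alternate-day administration is a superior method of administration with better continuity than the daily administration method". It then cautions that better continuity need not bring a survival benefit, and introduces the rules with "the decision criteria for selecting either study arm for future Phase III trials shall be as follows".

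The design basis is in section 13.3. It does not say which arm is expected to win: "Assume that 55% of the patients in the better group and 40% of the patients in the worse group complete treatment for 6 months". The size follows from this: "Based on the selection theory, 37 cases in each group are required to detect this 15% difference with a 90% probability of correct selection". The total then allows for losses: "Assuming dropout cases, a total of 100 cases are required". No significance level, sidedness or superiority hypothesis appears in the protocol.

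The rules in 13.4 apply to either arm. Rule (1) finds neither arm promising if both are below 40%. Rule (2) begins "If the completion rate of six-month treatment in one group exceeds 40% and is more than 15% higher than that in another group", and the arm it picks "is the most promising adjuvant chemotherapy in the study and is more suitable for the administration of S-1 in future Phase III trials". Rule (3) covers gaps of up to 15 points and turns to toxicity, quality of life, cost and outcome.

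**The concern.** A study designed to verify superiority needs a null hypothesis, a stated limit on the chance of a false claim, and a size that follows from both. A selection design has none of these by construction. It ranks arms reliably when a real gap exists and accepts that some arm may be picked when there is none. The opening sentence of 13.4 claims the first kind of design, while 13.3 and the rules supply the second.

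What is at stake is how the primary endpoint is read. If rule (2) picks alternate-day, the protocol holds two descriptions of that result: the rule's own, a schedule chosen for phase III, and the opening sentence's, superiority verified. Only the rule's description fits the design.

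**Working it through.** **Inputs.** From 13.3: completion of 55% and 40%, 37 per arm, 90% probability of correct selection, 100 patients in total. From 13.4: rule (2) needs an observed rate above 40% and a lead above 15%. I read the lead as percentage points, because 13.3 calls 55% against 40% a 15% difference. Equal allocation is inferred from the equal group sizes. The dropout rate is not stated; 74 evaluable of 100 would imply 1 − 74/100 = 26%. I therefore bracket the analysed size between 37 and 50 per arm.

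**1. The plan's own figure.** Picking the arm with more completers, with ties split equally, gives

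PCS = P(X₁ > X₂) + ½·P(X₁ = X₂), with X₁ ~ Bin(n, 0.55) and X₂ ~ Bin(n, 0.40).

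- n = 36: 0.8786 + ½ × 0.0413 = 0.8992
- n = 37: 0.8824 + ½ × 0.0398 = 0.9023

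Of the two, 37 reaches 90% and 36 does not, so the stated size reproduces. No significance level enters the formula.

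**2. Rule (2) when the arms are equal.** I summed the exact binomial probability of every outcome pair in which one arm's observed rate exceeds 40% and its lead exceeds 15 points, with the same true rate in both arms.

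| True rate, both arms | Alternate-day named, n = 37 | Either arm named, n = 37 | Alternate-day named, n = 50 | Either arm named, n = 50 |
|---|---|---|---|---|
| 40% | 9.3% | 18.6% | 6.0% | 12.0% |
| 47.5% | 10.0% | 20.0% | 6.6% | 13.3% |
| 50% | 10.0% | 20.1% | 6.7% | 13.3% |
| 55% | 9.9% | 19.8% | 6.6% | 13.1% |
| 60% | 9.6% | 19.1% | 6.3% | 12.5% |

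**3. A lead that just qualifies.** With 50 per arm, 15 points is 7.5 patients, so the smallest qualifying lead is 8. Take 28/50 (56%) against 20/50 (40%).

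- Difference 0.16; SE = √(0.56×0.44/50 + 0.40×0.60/50) = 0.0986
- 95% CI: 0.16 ± 1.96 × 0.0986 = −0.033 to +0.353
- Pooled z = 0.16/√(2×0.48×0.52/50) = 1.60, one-sided p = 0.055

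With 37 per arm, 20/37 against 14/37 gives 16 points, 95% CI −6 to +39, one-sided p = 0.081. These are examples. The same 8-patient lead at 21/50 against 13/50 gives p = 0.046, so the p-value depends on where the rates lie.

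**4. What a superiority test would have done.** Take a one-sided 5% level as an assumption. Then

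power = Φ[(0.15 − 1.645·√(2×0.475×0.525/n)) / √((0.55×0.45 + 0.40×0.60)/n)].

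- n = 37: Φ[(0.15 − 1.645×0.1161)/0.1148] = Φ(−0.36) = 36%
- n = 50: Φ[(0.15 − 1.645×0.0999)/0.0987] = Φ(−0.14) = 44%

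At two-sided 5% the figures are 25% and 32%. For 80% power the one-sided test needs 136 per arm and the two-sided test 173.

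**The case against.** The strongest reply is that nothing operative in the protocol concludes superiority. Where 13.4 fixes what follows from the data, it uses phase II selection language. The stated purpose in sections 0.2 and 1 is to evaluate tolerability and efficacy, and section 2.3 speaks of comparing durability. Only one sentence, in a translated document, speaks of verifying superiority. Selection designs omit a significance level on purpose, and the size is right.

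Most of this stands. It places the fault in one sentence and leaves the sample size and rules alone. It does not remove the fault: that sentence says what the study was designed to do, in the section that governs how the primary endpoint is interpreted. The caution after it concerns survival and does not qualify the claim about continuity.

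A reader might go further and infer that the trial has no control at all over false claims, because selection at 90% with 37 per arm corresponds to a test with a critical value of zero and a one-sided level near 50%. The documents do not support that. It describes simply picking the arm with more completers, whereas rule (2) also demands a lead above 15 points and a rate above 40%, and so has the much lower false-selection rate shown above. That rate is unstated, not absent. Nor is the missing significance level a gap in itself, since a selection design needs none.

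A significance level in a separate analysis plan would not settle the matter, because the size fixed here gives little power for such a test at conventional levels. How the difference is estimated and reported is ordinary analysis-plan content and forms no part of this point.

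**Conclusion.** The point holds in limited form: the opening sentence of 13.4 gives the study a property that its design does not have. The selection design is internally sound for its purpose, with a probability of correct selection of 0.902 at 37 per arm.

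A selection under rule (2) is a reasonable basis for choosing a phase III schedule, but it does not verify superiority. The results rest on equal allocation, independent binomial outcomes, a lead read in percentage points, 37 to 50 analysed per arm, and equal true completion somewhere in 40–60%. The power figures also rest on significance levels that I assumed.

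It would be wrong to conclude that the protocol itself will declare superiority. None of its rules does so. The risk is that the opening sentence is used to describe a selection result.

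**What to change.** Replace the first sentence of 13.4 with a selection aim, for example: *This is a randomised selection study to choose the S-1 schedule for a future phase III trial; selection under rule (2) is not evidence that one schedule is superior.*

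Beside rule (2), state how often it selects when the schedules are equal: about 6–7% per arm at 50 per arm and 9–10% at 37 per arm, or 12–13% and 19–20% for either arm, for true completion of 40–60%.

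The cost is a wording change and one added line. The sponsor gives up the claim to verify superiority, which this design could not support in any case. The sample size and the three decision rules stay unchanged.

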## 14. Discontinuation of the study

Enrollment will be terminated when the expected number of enrolled patients is reached, but enrollment will be accepted for eligible patients who have already been informed of their participation in the study at that time. If, during the course of the study, it is determined that patient safety is seriously compromised and the entire study must be terminated due to a serious adverse event or new information on the study drug or treatment, the Data and Safety Monitoring Committee will recommend to the principal investigator that the study should be terminated. The principal investigator will review the recommendation and make a decision to discontinue

the study with the approval of the Clinical Trial Review Committee. After the decision to discontinue the study, the principal investigator will promptly inform the participating institutions of the discontinuation and the reason for discontinuation in writing.

